## Abstract

**Background:**

Breast cancer is the leading cancer affecting women in Singapore. Its survivors commonly experience decline in physical function and quality of life post-mastectomy, due to their upper limb morbidity and wound issues. Rehabilitation can address the aforementioned issues. When rehabilitation is accessible and easy to adhere, it can optimize recovery.

Home-based tele-rehabilitation guided by healthcare professionals and self-managed by patients can potentially optimize the patients’ adherence to rehabilitation and recovery. With that in mind, a team of breast cancer specialists (oncologists, nurses, and therapists) in Singapore has developed one of the first tele-rehabilitation systems for local women undergoing a unilateral mastectomy. To our knowledge, no such systems have been evaluated or proven effective as a treatment option among local breast cancer patients with acute disabilities.

**Methods:**

This is a pilot quasi-experimental trial that aims to evaluate the feasibility of tele-rehabilitation and tele-drain care compared to usual care. Up to 40 patients (20 per group) will be recruited for this trial. They will be assigned to an intervention group that receives rehabilitation via a tele-rehabilitation system or a control group that receives rehabilitation in person at their clinic. The primary outcome of this trial is rehabilitation participation (i.e., the time spent on rehabilitation). The secondary outcomes are upper extremity functioning, perceived health, and quality of life.

**Discussion:**

As part of this pilot trial, patients who opt in for the tele-rehabilitation will be asked to share their experience with and thoughts on the tele-rehabilitation system. With the evidence obtained from the tele-rehabilitation patients of this trial, we will be able to improve the current system for our future trial. Further, our additional data on rehabilitation participation, physical function, and quality of life will help us design a sufficiently powered future main trial.

**Trial registration:**

The trial was approved by the National Healthcare Group’s Domain Specific Review Board (#2019/00283) and registered with www.ClinicalTrials.gov (#NCT04269967) in February 2020.

## Background

Breast cancer is the leading cancer affecting women in Singapore. It accounts for approximately 30% of cancer diagnosis among women in the nation [1]. The majority of breast cancer diagnoses in Singapore are at stage 1 and 2 with a high 5-year survival rate [1]. Treatment recommendations for breast cancer depend on various factors (e.g., stage of the cancer, size of the tumor, and personal preferences). In early stage of breast cancer, surgical procedure (such as lumpectomy or mastectomy) is often the first treatment option to be recommended. Further, women may elect to undergo mastectomy for different reasons (such as their hesitance toward radiation therapy and fear of recurrence) [2, 3]. Rates of mastectomy ranged from 43 to 59% locally between 2001 and 2010 [4]. Most breast cancer survivors experience decline in physical function and quality of life (QoL) due to their upper limb morbidity and wound issues after mastectomy [5].

Rehabilitation (e.g., physical and occupational therapy) is known to maintain or improve physical function and QoL [6]. It can address common issues (e.g., lymphedema, decreased endurance, and joint stiffness) that breast cancer survivors may experience after their surgery. For example, individuals with primary carcinoma who participated in post-surgery rehabilitation in a non-randomized controlled trial showed a significant improvement in various functional outcomes as compared to those who did not participate in any rehabilitation [7]. The outcomes included physical, cognitive, and social functions [7]. The current post-surgery care for breast cancer patients in Singapore includes arm exercises, arm and hand care, and self-arm massage [8].

When rehabilitation (services) is accessible and easy to adhere, it can optimize patients’ recovery post-surgery. However, a Singaporean mixed methods study of 70 patients discharged from inpatient rehabilitation found their common intention to discontinue their rehabilitation after their hospital discharge due to foreseeable barriers (e.g., accessibility, cost, and inconvenience), while the majority acknowledged the benefits of rehabilitation [9].

Telemedicine (or telehealth) refers to the use of telecommunications and technology to deliver health services (e.g., rehabilitation) outside of traditional settings (e.g., patients’ home) [10]. Tele-rehabilitation (a home-based telehealth service) guided by healthcare professionals and self-managed by patients can potentially provide a solution to the aforementioned barriers, which may lead to improved participation in rehabilitation after hospital discharge [11]. A few telemedicine studies reported that individuals who were diagnosed with breast cancer and received their rehabilitation using telecommunications and technology showed an equal or a higher amount of improvement in their health status compared to those who received their rehabilitation in a traditional way [12–14].

### Aims

The first aim of this study is to gather preliminary evidence for the feasibility of a tele-rehabilitation and tele-drain care among women who undergo a unilateral mastectomy for breast cancer. The second aim is to understand the lived experience of breast cancer diagnosis, treatment, and recovery process.

## Methods

### Study design

This is a pilot quasi-experimental trial. Patients will be placed into the intervention group (tele-rehabilitation) or control group (usual rehabilitation care) based on their preference. The total length of the study period will be 15 weeks; patients will undergo a 3-week drain care period (post-surgery) which will be followed by a 12-week rehabilitation period. A baseline assessment will be conducted prior to commencing rehabilitation (approximately 3 weeks from the surgery) and a follow-up (exit) assessment will be conducted at the end of their rehabilitation period (approximately 12 weeks from the baseline assessment). An additional qualitative study is embedded within the trial to gain a deeper understanding of the lived experience of women who are diagnosed with breast cancer to achieve the second aim.

### Patients (participants)

We plan to recruit up to 40 patients (20 per group) from the Singapore General Hospital (SGH) and National Cancer Centre Singapore (NCCS), where they will be receiving preoperative, surgical, postoperative, and rehabilitation care. Patients are recruited from multiple clinics, under a single healthcare system in Singapore, consisting of a multi-ethnic Asian population.

Patients are eligible to participate in the trial when they meet the following four criteria: (i) female 21 years of age and older, (ii) undergoing or underwent a recent unilateral breast surgery (wide excision or simple mastectomy) with lymph nodes removed, (iii) speak and write English or Mandarin, and (iv) no past or active psychiatric condition as assessed by a referring clinician. Patients are ineligible to participate if they meet one of the following four criteria: (i) having breast reconstruction, (ii) having legal blindness or severe visual impairment, (iii) having life expectancy of less than 3 months, or (iv) having previous upper limb injury or conditions that limit upper limb range of motion (shoulder flexion (< 150°) or elbow extension/flexion (< 0/145°) respectively).

### Procedure (recruitment, allocation, and data collection)

Potential participants will be approached by a breast care nurse and/or doctor (who will be providing the patient care related to breast cancer and mastectomy) during their pre-operation counseling session. These nurses and doctors will provide their patients with our study invitation letter. The patients will be asked to contact the research team directly using the contact information provided in the study invitation letter if they are interested in the study. Alternatively, if the patients agree, the nurses and doctors will obtain patients’ contact information (i.e., first or last name with an email address or a phone number only) which will be forwarded to the research team to initiate contact.

If patients agree to participate in the trial, they will complete the informed consent process with a trained member of the research team. The informed consent process can occur anytime between the time of their surgical consultation and 5 days post-surgery. After the informed consent process is completed, patients will self-assign themselves to the intervention group (tele-rehabilitation) or the control group (usual rehabilitation). The prescription and administration of drain care (education) and rehabilitation for both groups of patients are determined and managed by an assigned nurse and therapist per usual practice.

All consented patients will be asked to complete two assessments with a trained member of the research team at their home (or at the university where the research is being conducted). The first (baseline) assessment will take place approximately 3-week post-surgery after completing drain-care (education) period (i.e., pre-rehabilitation assessment). The second (exit) assessment will take place after completing a 12-week physical rehabilitation period (i.e., post-rehabilitation assessment) (refer to Fig. 1 for an overview of the study outlining the timing of baseline and exit assessments). No patients, care providers, assessors, or analysts will be blinded. Any adverse events, although unanticipated, will be discussed within the team and reported to the National Healthcare Group Domain Specific Review Board within seven calendar days.

**Fig. 1 Fig1:**
[figure not shown]
An overview of the study

### Tele-rehabilitation (intervention) and usual care (control)

Patients in the intervention group will have the tele-rehabilitation system for up to 15 weeks. The first 3 weeks will be for drain care video education (post-mastectomy) and the following 12 weeks will be for physical tele-rehabilitation (including shoulder and arm exercise, and self-arm massage). During the physical rehabilitation period, patients (in the tele-rehabilitation group) and/or an assigned occupational therapist may arrange up to five 30-min video conferences (the number of sessions will be determined by an assigned therapist, as per request or per need of each patient).

Patients in the control group will receive the same instructions (for drain care education as well as shoulder and arm exercise and self-arm massage) by their multidisciplinary rehabilitation team but without remote support with the tele-rehabilitation and tele-drain care system. Their drain care education and physical rehabilitation sessions will instead take place in-person at their clinic with their assigned nurse and therapist (refer to Table 1 for brief descriptions of drain care education with a nurse and rehabilitation with an occupational therapist).

**Table 1 Tab1:** Brief descriptions of drain care education with a nurse and rehabilitation with an occupational therapist

Drain Care Education	Arm and Shoulder Massage	Exercise
Drain care education provides information on how to manage the drainage devices and fluids collected post-mastectomy. These include proper and safe physical handling of the drainage devices, and proper sequences to empty, measure, and dispose fluids from the drainage devices.	Arm and shoulder massage are performed with the aim of managing edema (reducing arm swelling) post-mastectomy. They consist of a series of actions to facilitate pushing fluid out of the affected areas back into the bloodstream, therefore preventing fluid accumulation and limb swelling.	The exercises are performed with the aim of maintaining the active range of motion of the upper limbs, which concurrently helps to drain fluid. The exercises involve deep breathing and a series of movements including shoulder elevation, retraction, protraction and flexion, and elbow flexion and extension.
**Sample Instructions**		
Step 1. Wash your hand Step 2. Prepare your requisites Step 3. Drain fluid for measurement Step 4. Measure and record the amount of fluid drained, before disposal (twice a day)	Step 1. Take a deep breath Step 2. Place your affected arm on your shoulder with your elbow pointing to your side Step 3. Using the other hand, place it below your armpit Step 4. Gently sweep downwards past your waistline Step 5. Please ensure your palm has good contact with your body as you sweep downwards Step 6. Repeat this 20 times *Note. The arm/hand doing the massage is the contralateral side massaging the affected side.*	Step 1. Begin the exercise by clasping both hands and bringing them to the chest Step 2. Slowly bring both arms forward, making sure that your elbows are straight Step 3. Repeat this 5 times

### Measurements

A pilot study is conducted to test a set of feasibility objectives to warrant the viability of the main trial [15]. Based on an expected attrition or non-response rate, it is common to inflate the trial sample size for 10-20% [16]. The primary outcome of our pilot feasibility study is patients’ participation in the study and prescribed rehabilitation (i.e., the time spent on rehabilitation). It is a process assessment where both groups of patients will be asked to keep records of their participation in rehabilitation using a diary (logbook). The data on rehabilitation (e.g., the number of the rehabilitation sessions that they have and the duration of each session) will be collected once at the post-rehabilitation assessment (i.e., the study participation rate). Further, our tele-rehabilitation system will track the frequency and duration of the system use for the intervention group. The attrition rate of 20% or less (or the completion rate of 80% or above) is considered the criterion for the success of feasibility for our study.

In addition, all patients will be asked to complete a semi-structured qualitative interview about their experience with the recent diagnosis, rehabilitation, and recovery process at the end of the trial (after the 12-week rehabilitation period). For the additional qualitative interview, patients will be asked a series of simple open-ended questions which may include the following: (1) tell us about how you navigated your diagnosis, (2) how do you describe rehabilitation that you participated in over the past 12 weeks, and (3) how has your recovery process been—as expected or unexpected? The interview data will be digitally recorded with the patient’s permission and transcribed for qualitative analysis.

The secondary outcomes of this trial are upper extremity functioning, perceived health, and QoL. Upper extremity functioning will be measured by shoulder active range of motion (AROM) [17], arm circumference (AC) [18], the Quick Disabilities of Arm, Shoulder & Hand (QuickDASH) [19]. Perceived health will be measured by the EuroQoL-5D (EQ-5D-3L) [20] and QoL will be measured by the European Organization for Research and Treatment of Cancer Quality of Life Questionnaire Core 30 (EORTC QLQ-C30) [21]. For the secondary outcomes, all patients will be asked to complete all five measures with a trained member of the research team at both pre- and post-rehabilitation assessment. We hypothesize that both groups will show similar improvements across all secondary outcome measures.

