### Analysis

For quantitative data, we will report means and standard deviations for parametric data, medians and inter-quartile ranges for non-parametric data, and numbers and percentages of all categorical variables for descriptive purposes. Further, inferential statistics (e.g., *T* test, chi-square test) will be performed to compare the outcome measures between the two groups. We will perform a random data (entry) check by the secondary data management personnel (who did not collect the data or complete the initial data entry). Missing data will not be replaced or imputed.

For the qualitative data, we will conduct inductive analysis that involves discovering patterns, themes, and categories related to the lived experience of breast cancer diagnosis, rehabilitation, and recovery process (using five steps of qualitative data analysis outlined by Miles and Huberman) [28].

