### A power calculation

The data obtained from this pilot trial will be used to estimate a sufficient sample size for our future main trial. The existing literature suggests the minimum sample size of 10 to 15 participants per group [29] or 10% of a main trial’s sample size [30] to be sufficient for a pilot feasibility study. Considering such evidence, we plan to recruit a minimum of 10 and a maximum of 20 patients per group for this pilot trial.

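### Diary-based rehabilitation time, the primary outcome, is collected only at the exit visit, so it will exist only for patients who attend and is likely, though not certain, to be overstated

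*Protocol article*

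**What the plan says.** The Measurements section defines the primary outcome as "patients’ participation in the study and prescribed rehabilitation (i.e., the time spent on rehabilitation"). For the time component, "both groups of patients will be asked to keep records of their participation in rehabilitation using a diary (logbook"). The session counts and durations "will be collected once at the post-rehabilitation assessment (i.e., the study participation rate").

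The Procedure section fixes when that visit happens: "The second (exit) assessment will take place after completing a 12-week physical rehabilitation period". The Analysis section adds: "Missing data will not be replaced or imputed".

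Two further statements in Measurements bear on the point. One is a second data source: "our tele-rehabilitation system will track the frequency and duration of the system use for the intervention group". The other is the feasibility criterion: "The attrition rate of 20% or less (or the completion rate of 80% or above) is considered the criterion for the success" of feasibility.

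On size, the section on the power calculation says "we plan to recruit a minimum of 10 and a maximum of 20 patients per group for this pilot trial". Patients choose their own group (Study design; Procedure), and the Analysis section plans inferential tests between groups. The Discussion says the participation data will help design the main trial.

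**The concern.** In most trials the reason for dropping out and the outcome are separate things. Here the outcome is participation, so whether a value is missing is plausibly tied to the value itself. A patient who leaves before the exit visit hands in no diary, the rule on missing data leaves the gap open, and the mean is taken over those who stayed. If leavers did less rehabilitation than completers, the reported mean is too high.

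Two uses of the data are exposed. The first is the estimate of rehabilitation time carried into the design of the main trial. The second is the between-group comparison: groups formed by preference may lose patients at different rates, and the group that loses more would then look better than it is.

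The Measurements section also attaches the label of a study participation rate to the session data. A rate in that sense needs all enrolled patients in its denominator, and the diary data as collected do not supply them.

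**Working it through.** **Figures in the plan.** No power-based figure exists to reproduce; the size rests on a cited rule of thumb. The simple arithmetic agrees: 2 × 20 = 40 patients, and 1 − 0.20 = 0.80 completion.

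**Diaries at the tolerated attrition.** At 20% attrition, 0.8 × 20 = 16 diaries remain in a group of 20 and 0.8 × 10 = 8 in a group of 10. With 20 per group, up to 4 per group (8 of 40) have none.

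**Formula.** Let d be the share of patients without an exit diary and f the ratio of their mean rehabilitation time to that of completers. The all-patient mean, in units of the completer mean, is (1 − d) + d × f. The overstatement factor is therefore 1 / [(1 − d) + d × f]. The value d = 0.20 is the limit in Measurements. The protocol gives no value for f, so f is an assumption and is shown over a range.

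| d | f | (1 − d) + d × f | Completer mean / all-patient mean |
|---|---|---|---|
| 0.20 | 0 | 0.800 | 1.25 |
| 0.20 | 1/3 | 0.867 | 1.15 |
| 0.20 | 0.5 | 0.900 | 1.11 |
| 0.20 | 0.75 | 0.950 | 1.05 |
| 0.20 | 1 | 1.000 | 1.00 |
| 0.20 | 1.25 | 1.050 | 0.95 |
| 0.10 | 0 | 0.900 | 1.11 |
| 0.10 | 0.5 | 0.950 | 1.05 |

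The case f = 1/3 corresponds to leavers who stop at week 4 of 12 after exercising at the completers' weekly rate (4/12). The last row for d = 0.20 shows that the error reverses, to about 5% too low, if leavers did a quarter more than completers.

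**Comparison between groups.** Take an assumed attrition of 30% in one group and 10% in the other, with equal true participation over all patients and the same f in both. The completer means then differ by:

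- f = 0: (1/0.70) / (1/0.90) = 1.429 / 1.111 = 1.29
- f = 0.5: (1/0.85) / (1/0.95) = 1.176 / 1.053 = 1.12

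Put the other way, with f = 1/3 the all-patient means are 0.70 + 0.30/3 = 0.80 and 0.90 + 0.10/3 = 0.933 of a common completer mean. Their ratio is 0.80/0.933 = 0.857, so a true shortfall of 14% in the group with the higher loss would appear as no difference. With equal attrition and equal f in both groups, the ratio between groups is not distorted.

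**The case against.** A reader might infer that early leavers are the lowest participants by definition, so that participation is certainly overstated. The documents do not support that. Leaving the study is not the same as stopping rehabilitation: the Procedure section says that rehabilitation in both groups is managed by the assigned nurse and therapist as in usual practice. A patient may decline only the exit visit after a full course. Conversely, a patient who does almost nothing but stays enrolled is still asked to attend and is counted with her low value. The bias is zero if f = 1 or if every diary is returned. This objection stands, and it limits the claim to a likely bias of unknown size.

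A reader might also infer that all of the primary outcome is measured in completers only. That goes too far on two counts. The study-participation part is judged by attrition or completion, which already counts non-completers. The system log does not depend on the exit visit. However, the log exists in one group only and records use of the system, not all rehabilitation time. Filling gaps from it would measure the two groups with different instruments.

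A third objection is that no stated feasibility decision depends on minutes or sessions, and that a comparison of 10 to 20 self-selected patients per group is confounded and imprecise anyway. This stands as an argument about importance. It does not remove the effect on the time estimate passed to the main trial.

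Finally, the article does not say that diaries of withdrawn patients are discarded, and a fuller protocol may describe withdrawal procedures. But the article does not merely stay silent: it states a single collection, names the visit, and states the rule on missing data.

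**Conclusion.** The point holds in a limited form. Followed as written, the collection schedule and the rule on missing data make diary-based rehabilitation time a quantity known only for patients who attend the exit assessment. It is likely to be overstated, by between 0% and 25% at 20% attrition if leavers do between the same amount as completers and none at all. The between-group comparison is distorted as well if attrition differs: by a factor of 1.12 to 1.29 in the illustrative 30% versus 10% case with f from 0.5 to 0. Leavers' relative time and the attrition split are assumptions; the protocol gives neither. The control group is the more exposed, because it has no system log.

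The attrition criterion is not affected. The change is therefore recommended, not essential: it is cheap and improves data meant for the main trial, but no stated threshold for success turns on it.

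**What to change.** 1. Collect the diary (by photo, post or telephone) at withdrawal or at intervals, as well as at the exit assessment.
2. Summarise rehabilitation time over all self-assigned patients. Count recorded time up to the last diary date, and zero afterwards only where the patient is confirmed to have stopped rehabilitation. State in the Analysis section that such a zero is an observed value, so that the rule on missing data does not exclude it.
3. Where it is unknown whether a patient continued, give a sensitivity range from zero to the completer rate for the unrecorded period. With 20% of diaries wholly missing, the all-patient mean would run from 0.80 to 1.00 times the completer mean.
4. Use the diary, which both groups keep, for the group comparison, and the system log as a check on the diary within the tele-rehabilitation group. Report the completer mean as secondary.
5. Keep the term participation rate for a figure with all enrolled patients in the denominator.

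The cost is one remote contact per withdrawal and a few lines of analysis text. Some diaries will still be unobtainable, because patients may be unreachable or may decline, and the reported participation figure will probably be somewhat lower. The Trial status section says data collection is ongoing, so the change can still help for patients not yet at exit.

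### The plan hypothesises similar improvement on all secondary outcomes but names tests of difference; with 10 to 20 self-selected patients per group, a non-significant result cannot support that hypothesis

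*Protocol article*

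**What the plan says.** The Measurements section lists the secondary outcomes: shoulder active range of motion, arm circumference, QuickDASH, EQ-5D-3L and EORTC QLQ-C30, each taken before and after rehabilitation. It then commits to an expectation for all of them: "We hypothesize that both groups will show similar improvements across all secondary outcome measures".

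The Analysis section plans descriptive summaries and adds that inferential statistics, with the t test and chi-square test given as examples, "will be performed to compare the outcome measures between the two groups". On incomplete data it says: "Missing data will not be replaced or imputed".

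The section on the power calculation sets the size from pilot rules of thumb and concludes that "we plan to recruit a minimum of 10 and a maximum of 20 patients per group for this pilot trial". Under Study design, the groups are formed by choice: "Patients will be placed into the intervention group (tele-rehabilitation) or control group (usual rehabilitation care) based on their preference".

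The success criterion in Measurements is separate from all this: "The attrition rate of 20% or less (or the completion rate of 80% or above) is considered the criterion for the success of feasibility". The Discussion says that the data on participation, physical function and quality of life will help design an adequately powered main trial.

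**The concern.** A t test or chi-square test asks whether the data are incompatible with no difference. Here no difference is, in substance, what the investigators expect to find. The test can speak against that expectation but not for it, because a large p-value is equally what a small sample produces when a real difference exists. The hypothesis and the named method therefore do not fit each other, whatever the data turn out to be.

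The later use of the data gives this some weight. Whether the main trial should aim at superiority, non-inferiority or equivalence depends on what the pilot can say about function and quality of life. If a non-significant comparison were reported against a similarity hypothesis, it could look like confirmation while the interval still allowed a material disadvantage of tele-rehabilitation. Self-selection adds to this: differences between patients who prefer one mode or the other can create or hide a difference in outcome.

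**Working it through.** **The plan's own figure.** The 10 to 20 per group rests on literature rules of thumb (10 to 15 per group, or 10% of the main trial). No significance level, power, effect size or SD is given, so no formula can reproduce it. The one arithmetic check, 2 × 20 = 40, agrees with the stated total of up to 40.

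**Inputs from the protocol article.** n = 10 to 20 per group (A power calculation). Attrition of up to 20% counts as feasible (Measurements) and missing values are not imputed (Analysis). If 20% were lost in each group, 0.8 × 10 = 8 to 0.8 × 20 = 16 per group would be analysed.

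**Assumptions not in the article.** Two-sided 5% level, equal group sizes, a continuous outcome, and differences expressed in SD units. The article gives no expected difference, so a range is shown.

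**Step 1: how often the t test is non-significant.** Degrees of freedom are 2n − 2 and the noncentrality parameter is d × √(n/2), where d is the true difference in SD units. Power is the probability that a noncentral t variable exceeds the two-sided 5% critical value in absolute size. For d = 0.5:
- n = 20: noncentrality 0.5 × √10 = 1.581, critical value 2.024, power 0.338.
- n = 10: noncentrality 0.5 × √5 = 1.118, critical value 2.101, power 0.185.

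Probability of a non-significant result (1 − power):

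| True difference | n = 8 | n = 10 | n = 16 | n = 20 |
|---|---|---|---|---|
| 0.2 SD | 93% | 93% | 92% | 90% |
| 0.3 SD | 91% | 90% | 87% | 85% |
| 0.5 SD | 85% | 81% | 72% | 66% |
| 0.8 SD | 68% | 60% | 41% | 31% |

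With no true difference it is 95% at any n. Non-significance is thus the usual result for differences up to 0.5 SD, but not for 0.8 SD at the full 20 per group.

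**Step 2: precision.** The unadjusted 95% confidence interval half-width in SD units is t(0.975, 2n − 2) × √(2/n):
- n = 20: 2.024 × √(2/20) = 2.024 × 0.3162 = 0.64
- n = 16: 2.042 × √(2/16) = 2.042 × 0.3536 = 0.72
- n = 10: 2.101 × √(2/10) = 2.101 × 0.4472 = 0.94
- n = 8: 2.145 × √(2/8) = 2.145 × 0.5 = 1.07

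Even with an observed difference of exactly zero, the interval at 20 per group would run from −0.64 to +0.64 SD.

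**Step 3: would an equivalence analysis rescue the hypothesis?** The article gives no margin, so these are illustrations. Two one-sided tests at 5% each, with a true difference of zero and 80% power, need about 2 × ((1.645 + 1.282)/m)² patients per group for a margin of m SD. That is 191 for 0.3, 69 for 0.5 and 27 for 0.8 SD, all above 20. At 20 per group the power of that procedure is about 3% for a margin of 0.5 SD, 60% for 0.8 SD and 86% for 1.0 SD. Requiring the whole 95% interval to lie inside the margin is stricter: at 0.5 SD and 20 per group the power is about 0.2%.

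**The case against.** The strongest reply is that this is one sentence about secondary outcomes in a non-randomised feasibility pilot. The aim is preliminary evidence of feasibility, the size comes from pilot rules of thumb, and no power is claimed for these outcomes. All of that stands. A small sample is not an error in such a pilot, and the point is limited to pairing this hypothesis with these tests.

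The tests are given only as examples in a condensed article, and an analysis plan that is not shown may add a margin or an interval rule. That also stands, so the absence of a margin is not the complaint. It does not remove the mismatch between the hypothesis and the tests that are named, and at margins up to 0.8 SD an added equivalence test would not reach 80% power at 20 per group.

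The figures depend on the assumed difference. At 0.8 SD and 20 per group the t test has 69% power. Baseline adjustment would also narrow the intervals: with an assumed baseline–exit correlation r, the half-width at 20 per group shrinks by about √(1 − r²), from 0.64 to roughly 0.55 SD at r = 0.5 and 0.46 SD at r = 0.7. These points qualify the size, not the logic.

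A reader might infer two stronger claims that the article does not support:
- **That a non-significant result would be declared similarity and would decide whether the main trial goes ahead.** No section says that a large p-value will be read as similarity. Feasibility success is tied to attrition alone, and the data are said to help design and size the main trial.
- **That the many secondary outcomes make a false positive likely.** Ten independent tests at 5% would give 1 − 0.95¹⁰ = 40%. The article does not say that every movement on each arm is tested separately, and outcomes measured in the same patients are likely to be correlated, which would lower the figure.

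**Conclusion.** The point holds as a mismatch between a stated hypothesis and the named tests. The tests cannot support similarity, and at the planned size they would usually be non-significant for small to moderate true differences: 66% (20 per group) to 81% (10 per group) at 0.5 SD, or 72% to 85% if 20% are lost in each group. At 0.8 SD and 20 per group the figure is 31%. The unadjusted 95% interval half-width is 0.64 to 0.94 SD before attrition. These figures assume a two-sided 5% level, equal groups and a continuous outcome; unequal self-selected groups of the same total size would be less precise.

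The primary outcome and the attrition criterion are not touched. What is affected is what the secondary results may be said to show when they inform the design of the main trial. Severity is moderate: worth correcting before analysis, but not a fault that undermines the pilot.

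**What to change.** In Measurements, replace the similarity hypothesis with an exploratory objective: to estimate the between-group difference on each secondary outcome.

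In Analysis, state that for each continuous secondary outcome the baseline-adjusted between-group difference will be reported with its 95% confidence interval, and that a non-significant p-value will not be read as similarity. Add that the groups are self-selected, since baseline adjustment does not remove all differences between patients who choose one mode or the other.

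Leave any equivalence or non-inferiority margin, and its test, to the main trial. Justifying an important difference for every outcome, including each QLQ-C30 scale, is substantial work that the pilot does not need.

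The cost is a change of wording in two sections and a simple adjusted model, using baseline and exit measurements already planned. The article reports data collection as ongoing, so the change should be dated and made before the analysis. The downside is that the pilot will make no claim of similarity on secondary outcomes.
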